### Allocation

Participants are stratified based on their bone mineral density (BMD), assessed by dual-energy X-ray absorptiometry (DXA) at the hip and lumbar spine. Stratification follows WHO criteria, resulting in three main groups:

- Osteoporotic patients (T-score < -2.5 SD), further divided into fractured and non-fractured subgroups;- Osteopenic patients (-2.5 SD < T-score < -1 SD);- Healthy controls (T-score ≥ -1 SD).

A total of 120 participants are enrolled, with 30 individuals allocated to each of the four resulting subgroups (osteoporotic fractured, osteoporotic unfractured, osteopenic, and healthy). Allocation is performed upon confirmation of DXA availability and based on T-score values. No randomization is applied, as group assignment depends on predefined diagnostic criteria.

### Adverse events assessment process

As this is non-interventional no investigational study, treatments or procedures are administered to participants. Therefore, no adverse events directly related to the study protocol are expected. Standard clinical care will be maintained throughout the study period, and any medical events occurring during participation will be managed according to routine clinical practice. Nonetheless, any unexpected or relevant medical issues that arise during study-related procedures (e.g., during blood sampling) will be documented and reported in line with institutional policies and ethical guidelines.

### Data collection and management

Data are collected using a paper-based Case Report Form (CRF). In accordance with the General Data Protection Regulation (GDPR) – EU Regulation 2016/679 – and Clinical Trial Regulation 536/2014, all data within the project are recorded, processed, stored, and managed while ensuring data confidentiality through the implementation of appropriate technical and organizational measures.

### Statistical methods

Statistical analyses are performed using R software (12) and relevant packages, such as ggplot2 (13), for graphical data visualization. A p-value < 0.05 is considered statistically significant.

A total sample size of 120 patients (n = 30 per group) was calculated using G*Power software (power = 0.80, alpha error probability = 0.05). The estimation was based on a Chi-square test (contingency table) with a medium effect size (w = 0.33), derived from the hypothesized difference in PBMC viability (yes/no) between healthy, osteopenic, and osteoporotic patients (fractured and non-fractured). A 20% potential drop-out rate was also considered in the calculation. This sample size ensures adequate statistical power for the primary outcome while maintaining feasibility across the two recruiting centers.

All data are recorded in an electronic dataset comprising continuous variables (e.g., age, PBMC viability, cell count and size, T lymphocyte subpopulation percentages, expression of pro- and anti-inflammatory cytokines, platelet-related parameters, and bone turnover markers, including BMD T-score), nominal categorical variables (e.g., gender, diagnosis), and ordinal categorical variables (e.g., patient stratification). Univariate analyses are conducted to assess the distribution, central tendency (e.g., mean, median), and dispersion (e.g., standard deviation, variance, interquartile range) of quantitative variables, and the frequency distribution of qualitative variables. Continuous variables showing skewed distributions are transformed to approximate normality.

After assessing normality and homogeneity of variances, appropriate statistical tests are applied. For normally distributed data with equal variances, parametric tests such as ANOVA, General Linear Models (GLM), and Student’s t-test are used. In cases of non-normality or heteroscedasticity, equivalent non-parametric tests (e.g., Kruskal–Wallis and Mann–Whitney U tests) are employed.

Patients are stratified by BMD T-score and gender. Correlation, regression, and accuracy analyses are performed accordingly. Specifically, the relationship between BMD and PBMCs viability, count, size, differentiation, T lymphocyte subpopulations, inflammatory cytokines, platelet-related parameters, and serum biochemical markers of bone turnover is investigated. Pearson’s correlation coefficient is used for normally distributed data, and Spearman’s rank correlation is applied for non-parametric data. Receiver Operating Characteristic (ROC) curve analysis is conducted to assess the discriminative power of individual variables.

To avoid information loss and potential selection bias, missing values are imputed. When missingness is minimal, single imputation is used; otherwise, multiple imputations are performed, assuming data are missing at random (MAR) (14). Multiple imputation is conducted using the Multivariate Imputation by Chained Equations (MICE) package in R (15).

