
### Objectives and trial design

#### Primary objective

To analyze the viability, number, size, and differentiation time of PBMCs isolated from peripheral blood samples (2–5 ml) of non-osteopenic and non-osteoporotic patients (hereafter referred to as healthy patients), osteopenic patients, and osteoporotic patients (both fractured and non-fractured) with available DXA or, for fractured patients, DXA prescribed as per clinical practice for secondary prevention.

The aim is to evaluate the sensitivity and specificity of a diagnostic test based on the *in vitro* maintenance and differentiation of PBMCs (European Patent IOR No. 3008470, March 21, 2018) through a multicenter cross-sectional clinical study. Patients are stratified based on their BMD DXA T-score into osteoporotic, fractured and non-fractured (BMD T-score: < -2.5), osteopenic (BMD T-score: -2.5 < T-score < -1), and healthy (BMD T-score: ≥ 1). In accordance with secondary prevention guidelines, patients with a fragility fracture are categorized as ‘osteoporotic fractured’, irrespective of their exact BMD T-score. All assessments are conducted also considering specific gender differences.

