### Intervention

An overview of the study design and analytical workflow is shown in **Figure 1**. Healthy, osteopenic, and osteoporotic (fractured and non-fractured) patients of both sexes, with available DXA or, for fractured patients, DXA prescribed as per clinical practice for secondary prevention, are enrolled during outpatient visits and/or upon admission to the emergency department and/or hospital, after signing written informed consent. Subsequently, a blood sample (2–5 mL) is collected from each enrolled patient and used for PBMC isolation, performed through density gradient centrifugation, and for serum collection. Once isolated, a portion of PBMCs is cultured *in vitro* (without differentiation factors normally required for PBMCs viability maintenance and differentiation) to assess their viability, number, size, and differentiation into osteoclasts. PBMCs viability are evaluated using optical microscopy and the Alamar Blue assay (a non-toxic reagent that assesses cellular activity through the chemical reduction of resazurin to resorufin in the mitochondria of living cells) at 48, 72, and 96 hours and at 1 and 2 weeks. At the same time points, PBMCs number and size (diameter in µm) are also assessed. Finally, at 2 weeks, spontaneous osteoclastogenesis, i.e., the ability of PBMCs to spontaneously become osteoclasts, is evaluated and quantified through immunocytochemical analysis (Tartrate-Resistant Acid Phosphatase - TRAP - staining) and gene expression analysis *via* RT-PCR (Tumor Necrosis Factor alpha - TNF-α, Receptor Activator of Nuclear Factor κB Ligand – RANKL, Macrophage Colony-Stimulating Factor - M-CSF, Parathyroid Hormone - PTH). Differences in PBMCs viability, number, size, differentiation, and/or activity are also be analyzed considering gender differences. To achieve the secondary objectives of the protocol, a PBMCs aliquot undergoes immunophenotypic characterization to identify the T lymphocyte cell phenotype and evaluate its subpopulations. Specifically, the Th1 (CXCR3, CCR5), Th2 (CRTH2, CCR4, CCR3), Th17 (CCR6 and RORC), and TReg (CD25, CD26, CD127low) subpopulations are analyzed by flow cytometry. Biochemical levels of pro- and anti-inflammatory cytokines are assessed in serum samples from enrolled patients (interleukin (IL)-1, IL-2, IL-3, IL-4, IL-5, IL-9, IL-10, IL-17, IL-21, IL-22, IL-33, TNF-α, Interferon gamma - IFN-γ). Moreover, serum samples are also used to evaluate key markers of bone turnover, including bone-specific alkaline phosphatase, procollagen type I N-terminal propeptide (markers of bone formation) and N- and C-terminal telopeptides of collagen I (markers of bone resorption).

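### The primary objective names four PBMC measures, the sizing covers one viability test without a time point, and a single unadjusted p < 0.05 applies throughout, so the primary-objective error rate is not held at 5%

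*Protocol article*

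**What the plan says.** Four parts of the protocol article bear on this point.

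- **Primary objective.** It opens: "To analyze the viability, number, size, and differentiation time of PBMCs isolated from peripheral blood samples". The groups are healthy, osteopenic, osteoporotic fractured and osteoporotic non-fractured. The same section adds a second element: "The aim is to evaluate the sensitivity and specificity of a diagnostic test".
- **Intervention.** Viability is read "at 48, 72, and 96 hours and at 1 and 2 weeks". The text continues: "At the same time points, PBMCs number and size (diameter in µm) are also assessed". Differentiation into osteoclasts is quantified once, at 2 weeks.
- **Statistical methods, sizing.** The 120 patients (30 per group) come from one chi-square test on viability (yes/no) across the groups, with w = 0.33, alpha 0.05, power 0.80 and 20% drop-out. The section then states: "This sample size ensures adequate statistical power for the primary outcome". It names no time point for that outcome.
- **Statistical methods, testing.** The significance rule is unqualified: "A p-value < 0.05 is considered statistically significant". For normally distributed data with equal variances, "parametric tests such as ANOVA, General Linear Models (GLM), and Student’s t-test are used", with non-parametric equivalents otherwise. The article gives no order of testing, adjustment, decisive time point or exploratory label.

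**The concern.** Two sections disagree on what is primary. The objective puts four measures on the same footing, while the sizing treats viability alone as the primary outcome and does not say when it is read. The alpha of 0.05 behind the 120 patients belongs to one test, but the stated threshold lets any measure at any time be called significant at that level.

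What is at stake is the meaning of a positive result. If a report says that PBMC behaviour differs by stage of bone loss, the reader cannot tell whether that rests on the test the trial was sized for or on whichever of several readings fell below 0.05. In the second case the nominal 5% is not the error rate of the claim.

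**Working it through.** **Step 1. Reproduce the stated sample size.** Inputs from Statistical methods: w = 0.33, alpha 0.05, power 0.80. The degrees of freedom are not stated; four groups by yes/no gives (4 − 1) × (2 − 1) = 3. With non-centrality N × w², the smallest N reaching 80% power is 101 (101 × 0.1089 = 11.0). Adding 20% gives 101 × 1.2 = 121.2, rounded up to 122, which is within 2 of the stated 120. With df = 2 or df = 1, N is 89 or 73, and neither leads to 120. The design alpha is therefore the alpha of one four-group test. For that test, 120 evaluable patients give 87% power, and 96 (120 less 20%) give 78%.

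**Step 2. Count what the primary objective can generate.** One omnibus test per measure gives 4 tests. Viability, number and size at five times plus differentiation once gives 3 × 5 + 1 = 16.

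**Step 3. Independent tests.** The chance of at least one p < 0.05 when no true difference exists is 1 − 0.95^k.

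- k = 1: 5%
- k = 4: 1 − 0.95^4 = 18.5%
- k = 16: 1 − 0.95^16 = 56.0%

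**Step 4. Correlated tests.** Readings from one patient's culture are unlikely to be independent. The document gives no correlations, so a range is assumed. Normal outcomes were simulated in four groups of 30 with no true difference, with one-way ANOVA on each outcome.

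| Omnibus tests | Assumed correlation | At least one false positive |
|---|---|---|
| 4 | common, 0.5 | 17% |
| 4 | common, 0.8 | 12% |
| 16 | common, 0.5 | 39% |
| 16 | common, 0.8 | 22% |
| 16 | between times 0.3; between measures 0 to 0.5 | 49 to 53% |
| 16 | between times 0.5; between measures 0 to 0.5 | 44 to 49% |
| 16 | between times 0.7; between measures 0 to 0.5 | 38 to 43% |
| 16 | between times 0.9; between measures 0 to 0.5 | 27 to 32% |

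With the independent case as the upper end, this gives about 12 to 19% for one test per measure and roughly 20 to 56% for one per measure and time. Stronger correlation lowers both figures, but they fall to 5% only if the tests are perfectly correlated.

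**Step 5. Pairwise tests, if used.** Four groups give 4 × 3 / 2 = 6 pairs. If all six are tested uncorrected and without a prior omnibus test, viability at one time alone carries about 20%. Across all 16 outcomes the figure is 72 to 97% for between-time correlations from 0.9 down to 0. This is a conditional case, because the document does not say that pairs are tested in this way.

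**Step 6. Compare remedies.** Bonferroni over four measures (alpha 0.0125) would need 137 evaluable patients for 80% power at w = 0.33, and 120 would give 73%. One named primary test stays at alpha 0.05 and keeps the power in step 1.

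**The case against.** The strongest reply is that most of this is silence, and silence may be filled elsewhere. The article condenses a fuller protocol, and an analysis plan that is not shown may set the order of tests and the correction. The text also does not say that each time point is tested separately; the listed general linear model could handle time in one analysis. The two-sample tests may be meant for comparing the sexes, which is planned throughout. The aim is partly framed as estimating sensitivity and specificity, and nowhere does the article say that one significant measure establishes the primary objective. The sizing does point to one outcome.

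Much of this stands, and it limits the size of the point. A reader might infer from the list of measures, times and groups that a false primary finding is more likely than not. The document does not support that. Passing 50% with omnibus tests needs at least 14 independent ones (1 − 0.95^14 = 51.2%; 13 give 48.7%), and in the simulations the 16 tests stay below 50% once the correlation between times reaches 0.5. The much higher pairwise figures need ungated, uncorrected testing of all six pairs, which the article permits but does not state. If pairs were tested only after a significant omnibus test, the error rate under no difference at all could not exceed the omnibus rate.

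The reply does not remove the conflict between the four-measure objective and the one-outcome sizing, the missing time point for that outcome, or the unqualified threshold. The first and last are statements in the article, not omissions, and the choice of the primary outcome and its time belongs in the protocol.

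**Conclusion.** The point holds in a limited form. The primary objective and the sizing have to be reconciled, because the protocol does not fix which measure and which time are confirmatory while it declares any p below 0.05 significant. If more than one measure or time is tested under that rule, the error rate for a group difference in the primary objective is above the 5% used in the sizing: about 12 to 19% for four omnibus tests and roughly 20 to 56% for sixteen. These figures assume no true difference on any measure, normal outcomes, 30 evaluable patients per group and the correlations shown, none of which the document supplies. The direction does not depend on the correlations unless they are perfect; the size does. Uncorrected pairwise testing would raise the figures, but it is a possibility under the text and not a stated plan.

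**What to change.** Make the Primary objective and Statistical methods sections agree, and fix the choice while the data evaluators are still blinded to clinical status.

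1. Name the four-group test of PBMC viability, in the yes/no form used for the sizing, at one stated time point and by one stated reading method, as the only confirmatory group comparison. Use alpha 0.05.
2. Only if that test is significant, test the six group pairs and then number, size and differentiation, each at a named time. Use Holm adjustment or one fixed order. If Holm is chosen, treating the pairs and the three measures as one family of 6 + 3 = 9 avoids spending alpha twice.
3. Label other time points, by-sex comparisons, and all lymphocyte, cytokine, platelet and bone-turnover comparisons and correlations as exploratory. Report them with confidence intervals and without significance claims.
4. Serve the accuracy aim by reporting sensitivity and specificity, with confidence intervals, for the same viability measure at the same time point.

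The cost is a paragraph of wording. The primary test keeps the alpha and power it was sized for, and no patients are added. The downside is that fewer pairwise and secondary results can be called significant.

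### PBMC viability is yes/no in the sample size but continuous in the dataset and tests; with no positive-test rule stated, sensitivity and specificity could, as written, only come from a cut-off chosen in the same patients

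*Protocol article*

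**What the plan says.** All references are to the protocol article.

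- **Statistical methods, sample size.** The 120 patients come from a "Chi-square test (contingency table) with a medium effect size (w = 0.33"), based on a "hypothesized difference in PBMC viability (yes/no) between healthy, osteopenic, and osteoporotic patients". The paragraph closes by saying that this gives adequate power for the primary outcome.
- **Statistical methods, next paragraph.** The dataset is described as holding "continuous variables (e.g., age, PBMC viability, cell count and size" and others. Group comparisons use ANOVA, general linear models or t-tests, or their rank-based equivalents. No test for a binary outcome is named.
- **Intervention.** "PBMCs viability are evaluated using optical microscopy and the Alamar Blue assay", at 48, 72 and 96 hours and at 1 and 2 weeks. That is 2 methods × 5 times = 10 readings per patient.
- **Primary objective.** The study analyses viability, number, size and differentiation time, and aims to "evaluate the sensitivity and specificity of a diagnostic test based on the" in vitro maintenance and differentiation of PBMCs.
- **Secondary objectives and Statistical methods.** Accuracy analyses are announced. The only technique given is ROC analysis, applied to individual variables to judge how well they discriminate.

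**The concern.** Sensitivity and specificity are properties of a rule that calls each patient positive or negative. The sample-size paragraph assumes that such a call exists for viability. The rest of the section treats viability as a measurement, and the article does not say how one becomes the other: which method, which time, which direction, and what value counts as positive.

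With a continuous reading, an ROC curve and no threshold fixed in advance, the route left open is to read a cut-off from the curve of the patients in whom accuracy is then reported. That gives the apparent accuracy of a rule fitted to this sample, which is too high on average and can suggest discrimination where there is none. The test that justified 120 patients also has no stated counterpart in the analysis.

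**Working it through.** **1. Does the design calculation really use one binary result per patient?**

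Inputs (Statistical methods): "power = 0.80, alpha error probability = 0.05"; w = 0.33; four groups of 30; 20% drop-out. The degrees of freedom are not stated. A binary outcome across four groups gives df = (2 − 1) × (4 − 1) = 3.

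Formula: N = λ / w², where λ is the noncentrality at which the chi-square test has power 0.80.

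- df = 3: λ = 10.903 and w² = 0.1089, so N = 100.1, rounded up to 101. Drop-out as 101 × 1.2 gives 122; as 101 / 0.8 it gives 127. Taking 100 × 1.2 gives exactly 120.
- df = 2: N = 89, then 107 or 112.
- df = 1: N = 73, then 88 or 92.

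Only df = 3 with drop-out added as a factor of 1.2 comes to about 120. Power is then 0.873 with all 120 patients and 0.781 with the 96 left after 20% loss. So the figure of 120 reproduces, and it confirms that the design treats viability as one yes/no result across four groups.

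**2. Does the analysis match?**

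| Item | Sample-size paragraph | Following paragraphs |
|---|---|---|
| Scale of viability | yes/no | continuous |
| Test | chi-square | ANOVA, GLM, t-test or rank tests |
| Readings per patient | one | ten (Intervention) |
| Positive-test rule | implied | none stated |
| Accuracy method | not applicable | ROC of individual variables |

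**3. How large is the bias from an in-sample cut-off?**

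Assumptions that are not in the documents: normally distributed readings with equal variance in cases and non-cases; 60 osteoporotic v 60 other patients; cut-off at the maximum Youden index J (sensitivity + specificity − 1); no missing data; 1,500 runs per setting. For ten readings, equal true accuracy and pairwise correlation 0.5 or 0.8.

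True value: J = 2Φ(d/2) − 1 with d = √2 × Φ⁻¹(AUC). AUC 0.50, 0.65 and 0.75 give J = 0, 0.21 and 0.37.

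| True AUC | True J | Apparent J, one fixed reading | Apparent J, best of ten readings |
|---|---|---|---|
| 0.50 | 0 | 0.10–0.15 | 0.17–0.23 |
| 0.65 | 0.21 | 0.29 | 0.35–0.38 |
| 0.75 | 0.37 | 0.43 | 0.49–0.52 |

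In the no-signal row, the lower end of the one-reading range has the direction fixed in advance (0.10 to 0.11 between runs), and the upper end lets the data choose it. In the other rows direction makes almost no difference.

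Half the excess in J is the average inflation of sensitivity and specificity. At true J = 0.37, one reading gives (0.43 − 0.37) / 2 = 3 percentage points. The best of ten gives (0.49 − 0.37) / 2 = 6 to (0.52 − 0.37) / 2 = 7.5 points.

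Smaller comparisons fare worse: with 30 v 30 and no signal, one reading gives 0.15 with direction fixed and 0.21 with direction free.

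**The case against.** **The article condenses a fuller protocol.** A missing time point or threshold could sit in the full protocol, the analysis plan or the patent, so that omission alone would not be a finding. What stands is the conflict inside Statistical methods: one variable is both the binary primary outcome and a continuous variable with different tests. An unseen plan can add detail, but this text would still need reconciling.

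**The mismatch may be partly wording.** A yes/no microscopy call and a continuous Alamar Blue signal can coexist, and the lists of variables and tests are open-ended. A reader might infer that the yes/no outcome will never be analysed. The article does not show that; it only fails to say how it will be.

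**No data-driven selection is announced.** A reader might infer that the investigators will choose a cut-off, a direction and the best of ten readings from the data. No section says so, and an area under the ROC curve needs no cut-off. The supported statement is conditional: sensitivity and specificity are the aim, and nothing else in the text leads to them. The best-of-ten column shows what would happen if readings were also selected; it does not describe the plan. It also treats all ten as continuous.

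**The patent may already define the test.** A reader might infer that the index test is a viable or non-viable call under the light microscope. The Introduction mentions only observation by light microscopy, and the Primary objective bases the test on maintenance and differentiation. A viability call alone might not be that test, so the sponsor must define it.

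**The study is partly developmental.** The Introduction and Expected outcomes speak of developing and enhancing the patent, and apparent accuracy is a normal product of development. That stands as an argument for labelling; the Primary objective nevertheless promises sensitivity and specificity.

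**Blinding.** Blinding technicians and data evaluators helps with reading bias. It does not prevent an optimistic cut-off, because an ROC curve needs the diagnosis, even if coded.

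**Conclusion.** The concern holds in a limited form. Statistical methods contradicts itself on the scale and test of the outcome that justifies the sample size, and no stated step leads from the readings to the sensitivity and specificity that the study aims at. As written, those figures could only come from a cut-off chosen in the same patients.

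If they do, expect about 3 to 5 percentage points of inflation on the average of sensitivity and specificity for one reading at true AUC 0.70 to 0.80, over splits from 60 v 60 to 30 v 30. It is larger for a useless test: about 5 to 7.5 points at 60 v 60. These sizes rest on the assumed binormal model and on an assumed split, since the article does not say which groups count as positive. Viability is treated as primary because the sample size rests on it; the Primary objective names three further variables.

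The figure of 120 is not at fault: it reproduces on the binary scale, apart from drop-out apparently being added as × 1.2 rather than / 0.8.

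**What to change.** 1. Reconcile Statistical methods so that the primary outcome has one scale and a matching test. If it stays binary, list it as binary, name the test used for sizing, and list any continuous signal separately. If it becomes continuous, redo the sample-size statement on that scale.
2. Have the sponsor name one primary index reading, with method, time point, direction and rule for a positive result, consistent with the test defined in the Primary objective. State which groups count as diseased.
3. Lock that rule, with a date, before laboratory results are linked to diagnosis. Enrolment began in August 2024, so this should be done promptly.
4. Report sensitivity and specificity of the locked rule with confidence intervals.
5. Make the other methods and time points secondary. Label any ROC-derived cut-off exploratory and report it with bootstrap or cross-validated optimism correction. The correction must repeat every selection step, including any choice among readings.

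Cost: wording in the protocol and analysis plan; no new samples or procedures. The downside is that the headline accuracy may look less favourable than with an optimised cut-off.

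### Rank tests are the stated remedy for unequal variances but do not correct for them; the effect is slight at 30 per group and could be larger in comparisons involving sex

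*Protocol article*

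**What the plan says.** All of this is in the Statistical methods section of the protocol article, unless another section is named.

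- The classical tests are restricted to well-behaved data: "For normally distributed data with equal variances, parametric tests such as ANOVA, General Linear Models (GLM), and Student’s t-test are used".
- Everything else goes one way: "In cases of non-normality or heteroscedasticity, equivalent non-parametric tests" are used, and the examples named are Kruskal-Wallis and Mann-Whitney U. Non-normality and unequal variance therefore share one remedy. No variance-robust method is named anywhere in the article.
- Before any testing, skewed continuous variables are to be transformed towards normality.
- The significance rule is "A p-value < 0.05 is considered statistically significant".
- Group sizes by bone status are fixed at 30 in each of four groups (Allocation section). By contrast, "Patients are stratified by BMD T-score and gender", and the Objectives and Intervention sections say that the assessments will also take account of gender. No quota or expected number per sex is given.

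**The concern.** Calling the rank tests equivalent to ANOVA and the t-test means using them to decide whether groups differ in location. For that purpose they need the groups to have the same shape and spread under the null hypothesis. The plan turns to them when equal spread has just been judged not to hold. This is a stated remedy that does not treat the stated problem, so it is more than detail left to an analysis plan.

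A difference in spread alone can then raise the false-positive rate for a difference in PBMC count, size, viability as a continuous measure, or a cytokine. In the opposite configuration the test becomes conservative, rejecting well below 5% when nothing differs. Both effects grow when group sizes are unequal. The bone-status groups are equal by design, but nothing in the article makes the sexes equal within them.

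**Working it through.** **The plan's own figure first.** "A total sample size of 120 patients (n = 30 per group) was calculated using G*Power software", with "power = 0.80, alpha error probability = 0.05". "The estimation was based on a Chi-square test (contingency table) with a medium effect size (w = 0.33"), and "A 20% potential drop-out rate was also considered in the calculation". For yes/no viability across four groups, df = (4−1)(2−1) = 3 and the noncentrality is N·w².

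- At N = 101, 101 × 0.33² = 11.0 and power is 0.80.
- 101 × 1.2 = 121.2, or 122 rounded up, close to the stated 120. (101/0.8 would give 127.)
- With 20% lost, 120 leaves 96, and power is 0.78.

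The sizing rests on a chi-square test, so the point below does not alter it.

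**Inputs for the check.** Nominal level 0.05 and 30 per group come from the article. SD ratios (1.5 to 3) and sex splits within a group of 30 (18/12, 22/8) are assumptions. Data are normal with equal means, so every rejection is a false positive.

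**Why Mann-Whitney goes wrong.** The test divides U by a null variance that assumes identical distributions:

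V₀/(n₁n₂) = (n₁ + n₂ + 1)/12.

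For normal data with equal means and SDs σ₁, σ₂ the actual variance is

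V/(n₁n₂) = (n₁−1)·a + (n₂−1)·b + 1/4, with a = arcsin[σ₂²/(σ₁²+σ₂²)]/2π and b = arcsin[σ₁²/(σ₁²+σ₂²)]/2π.

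If σ₁ = σ₂, then a = b = 1/12 and V = V₀. Otherwise the approximate type I error is 2·[1 − Φ(1.96/√(V/V₀))].

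- **30 v 30, SDs 1 and 3:** a = 0.1782, b = 0.0159. V = 29(0.1782 + 0.0159) + 0.25 = 5.88 against V₀ = 61/12 = 5.08. Ratio 1.157, error 6.8%.
- **18 v 12, SDs 1 and 2:** a = 0.1476, b = 0.0320. V = 17(0.1476) + 11(0.0320) + 0.25 = 3.11 against V₀ = 31/12 = 2.58. Ratio 1.204, error 7.4%.
- **22 v 8, SDs 1 and 3:** V = 21(0.1782) + 7(0.0159) + 0.25 = 4.10 against 2.58. Ratio 1.589, error 12.0%.
- **22 v 8, SDs 3 and 1:** V = 21(0.0159) + 7(0.1782) + 0.25 = 1.83 against 2.58. Ratio 0.709, error 2.0%.

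**Simulation of the same quantities** (20,000 to 40,000 replicates) agrees:

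| Groups | SDs | Rank test | Welch |
|---|---|---|---|
| 30/30/30/30 | 1, 1, 1, 2 | 5.5% | 4.9% |
| 30/30/30/30 | 1, 1, 1, 3 | 6.1% | 4.8% |
| 30 v 30 | 1, 2 | 6.0% | 4.9% |
| 30 v 30 | 1, 3 | 6.9% | 5.0% |
| 18 v 12 | 1, 1.5 | 5.9% | 4.9% |
| 18 v 12 | 1, 2 | 7.4% | 5.3% |
| 22 v 8 | 1, 3 | 12.4-12.9% | 5.1-5.3% |
| 22 v 8 | 3, 1 | 2.0-2.1% | 4.9-5.0% |
| 24/24/24/10 | 1, 1, 1, 3 | 9.7% | 5.1% |
| 10/10/10/24 | 1, 1, 1, 3 | 2.4% | 5.1% |

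With a continuity correction the 22 v 8 figure is about 11.4%. The last two rows illustrate a four-group comparison within one sex, again with assumed numbers.

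**How likely is imbalance?** Without a quota, and with a true 50% share of each sex, the chance of exactly 15/15 in a group of 30 is 0.14, and 0.14446⁴ = 0.0004 for all four groups. A split at least as uneven as 22/8 has probability 1.6% at a 50% share, but about 43% if one sex makes up 70%. The article does not settle which applies.

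**The case against.** Much can be said for the plan, and most of it limits the weight of the point.

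- **The main comparison is hardly touched.** With four groups of 30, Kruskal-Wallis stays near 5.5-6%. It is closer to nominal there than ordinary ANOVA (8.2% for SDs 1, 1, 1, 3). This stands. It does not carry over to every pairwise comparison: at 30 v 30 with SD ratio 3, Student's t gives 5.2% and Mann-Whitney 6.9%.
- **The larger figures are built on assumptions.** No SDs and no numbers by sex are given. A reader might infer that the trial will run at an 11-13% false-positive rate by sex. The article does not support that, and mild imbalance with moderate heterogeneity gives 6-8%.
- **By-sex rank tests are inferred.** The sentence on stratifying by T-score and gender leads into correlation, regression and accuracy analyses. Comparing groups by sex with these tests follows from the repeated commitment to look at gender, but is not spelled out. Nor does the article specify a test of one group of 30 against the other 90 pooled, so no weight is placed on that contrast.
- **Transformation comes first, and the tests are given as examples.** Transformation may well reduce unequal spread in counts and cytokines, and the list is open. Yet where inequality remains, both tests named are the wrong kind.
- **Rank tests keep their level if the null is identical distributions.** That is true, but the article does not state that null, and presenting the tests as counterparts of ANOVA and the t-test points to location.
- **Welch is no cure-all.** On untransformed lognormal data with equal means it gave 14.6% at 8 v 22 (log-SDs 1 and 0.5) and 11.3% at 12 v 18. This stands and shapes the fix.

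**Conclusion.** The point holds in a limited form. The article prescribes, for unequal variances, tests that do not correct for them when read as tests of location. At the planned 30 per group the consequence is slight: about 5.5-7% against a nominal 5% for SD ratios of 2 to 3. Where sex makes group sizes unequal, the error could be about 6-8% under mild assumptions, 11-13% under severe ones, or about 2% when the larger group is the more variable. These ranges rest on normal data and on assumed SD ratios and sex splits. Transformation may reduce them.

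It would be wrong to conclude that the sample size, the chi-square comparison of yes/no viability, or the estimation of sensitivity and specificity is compromised, because none of these uses the faulted rule. That the sexes will be unequal is likely without a quota, but the article does not establish it.

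**What to change.** Replace the single sentence with a rule that separates the two problems, applied after any transformation:

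- Unequal variances: Welch's t-test or Welch's ANOVA, or a linear model with heteroscedasticity-robust standard errors.
- Marked non-normality with similar spread: Kruskal-Wallis or Mann-Whitney.
- Both together: Brunner-Munzel or a similar method. In the two-group simulations it stayed at 4.9-5.4%, apart from 5.0-6.3% at 22 v 8.

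The cost is small. When variances are in fact equal, Welch loses nothing noticeable at 30 v 30 (power 80.9% for both Welch and Student's t). At 8 v 22 it loses about 4 points (75.5% against 79.5%), which is similar to Mann-Whitney (75.2-76.8%), the test it would replace. Enrolment, sample size and data collection do not change.
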